**ad 4. SELFMONITORING**

Self-monitoring is an essential tool to improve compliance during a lifestyle program. It will be implemented using a PAM "stepcounter" to measure daily physical activity and the "eetmeter" ([www.voedingscentrum.nl](http://www.voedingscentrum.nl)). This webbased tool is used to give feedback on food intake, and caloric intake on a daily basis. Patients will be trained to use this device. A diary with sporting activities as well as caloric intake will be evaluated by the dedicated nurses.

**ad 5. INVOLVEMENT OF THE PARTNER**

Involvement of the partner and family of the women is important in order to guarantee social support and a "buddy system" during lifestyle changes.

**ad 6. REFERRAL**

When indicated, referral to psychologist or intervention available in the general health care system will used.

Patients undergoing the lifestyle program will be guided and supported by trained nurses or dieticians or nurse practitioners, who will be trained prior to the study. Women who miss two consecutive sessions and who are not willing to catch up in another group are excluded from the program.

The standardized lifestyle program consists of four sessions in the first three months, and than a booster of two sessions in the last three months. Telephone consultation or consultation by mail is scheduled in between these sessions four times. (see table 1)

**FOLLOW-UP:**

All participating couples (usual care arm and the experimental care arm) will complete several questionnaires, i.e. the SF-36: measuring satisfaction, the SQUASH list: for physical activity, the FFQ: food frequency questionnaire for assessing nutrient intake): a structured questionnaire about food pattern (e.g. breakfast yes/no) and important food components (e.g. snacks, fruits and vegetables and meat), the Dutch Eating Behaviour Questionnaire (DEBQ): for assessment of restrained, emotional and external eating behaviour (van Strien 1986). Finally, several questions are completed i.t.o. history of body weight, e.g. the duration of overweight, weight fluctuations.

Questionnaires are webbased. In case a patient does not use the computer paper questionnaires will be used. Questionnaires will be completed at start, 12 weeks, 24 weeks and 52 weeks after randomisation. In addition each woman will receive a questionnaire for details on associated direct costs of professional care and on indirect costs like transportation, sporting activity and productivity loss. These questionnaires will be handed out in consultation 1, week 1 of the lifestyle module or at the start of fertility treatment for

women that were randomised for “usual care”. This will be repeated at the time points of the other questionnaires (12, 24 and 52 weeks after randomisation and at the end of follow-up).

Finally, patients who get pregnant during the period up to 24 months after randomisation will receive a questionnaire in which they can register their (self-reported) weight-gain during pregnancy. To assess gestational diabetes, an oral glucose tolerance test is advised at 28-30 weeks of gestation. Cord blood will be taken from approximately 150 patients after childbirth to assess the epigenetic and metabolic profile. The data will also be used in the follow-up study in case women give informed consent to participate in the follow up study of her child: “the preconception weight loss; does it affect infant health study” (METc: 2011/134), (the so-called “Lifestyle-kids” study).

Moreover, we will register reproductive outcome, fertility treatments as well as the course and outcome of subsequent pregnancies, including obstetrical interventions for a period up to 24 months after randomisation.

## **6. METHODS**

### **6.1 Study parameters/endpoints**

#### **Background and Demographic Characteristics**

To assess whether the treatment groups were balanced, the study populations will be compared for baseline measurements including female age, education, ethnicity, type of infertility (primary/secondary), duration of infertility, intoxications, body mass index, as well as sperm analysis according to WHO standards.

#### **6.1.1 Main study parameter/endpoint**

The primary endpoint will be a healthy singleton of more than 37 week gestation born after vaginal delivery. The initial analysis, will be done by intention to treat, so we will not make a difference for treatment independent pregnancies and pregnancies that occurred after treatment. Patients who will drop out of the study will be analysed according to their group of randomisation. In a per protocol analysis drop outs will be asked to provide information on the primary outcome, i.e. live birth within two years after randomisation. These drop outs will be analysed as non-compliant.

#### **6.1.2 Secondary study parameters/endpoints**

Secondary outcome parameters are:

1. pregnancy outcome and -complications: miscarriage, gestational diabetes, Pregnancy induced hypertension, preeclampsia, HELLP, prematurity <37 weeks, macrosomia (>90

(Large for Gestational Age), induction of labour, prolonged duration of labour, operative delivery, assisted delivery and increased blood loss, and multiple pregnancies

2. percentage of women needing fertility treatment in both groups (OI, IUI, IVF, ICSI) and ongoing pregnancy rates in these treatments.

3. Quality and number of oocytes and embryos and cryo embryos resulting from an IVF or ICSI procedure and the amount of embryos per transfer and implantation rate of transferred embryos

4. complications during fertility treatment: ovarian hyperstimulation syndrome, infection, tubal pregnancies, torsion (etc).

5. perinatal outcome: stillbirth, pregnancy duration, body weight, Apgar scores, arterial pH, congenital anomalies and neonatal admission to a neonatal medium, high or intensive care unit..

6. quality of life, pre-pregnancy body weight, weight gain during pregnancy, waist circumference, behaviour influencing weight, i.e. nutritional habits and exercise pattern, blood pressure, glucose/insulin ratio (HOMA), hormonal profile (androgens, adipokines and cytokines) and costs.

#### **6.1.3 Other study parameters**

**ECONOMIC EVALUATION:** The aim of the economic evaluation is to compare the costs and health effects of a lifestyle program versus “usual care”. The analysis will be a cost-effectiveness analysis with the proportion of healthy singleton of more than 37 week gestation born after vaginal delivery as the primary outcome.

### **6.2 Randomisation, blinding and treatment allocation**

The randomisation is performed by computer at a central randomisation centre in the AMC. Randomisation will be stratified according to presence or absence of anovulation and center of treatment.

Women eligible for the study will be referred to a research nurse. This person is dedicated to counselling eligible patients and will perform randomisation and collect follow-up data, but will not perform the experimental intervention. We will collaborate with the research nurses who are involved in the obstetric and urogynaecological consortium. In this consortium, eight large randomised clinical trials are performed. Information on this infrastructure is obtainable from <http://www.studies-obsgyn.nl/>

### **6.3 Study procedures**

#### **RANDOMISATION BY RESEARCH NURSE**

Baseline measurement of body weight, length, waist, hip and blood pressure for all patients. A blood sample of 10 cc will be taken and serum stored of all patients.

Handout and introduction of the "eetmeter" and stepcounter and food and physical activity diary for the patients randomised for lifestyle intervention.

Website [www.voedingscentrum.nl/](http://www.voedingscentrum.nl/) eetmeter is explained.

## **TIME SCHEDULE LIFESTYLE PROGRAM**

(see flow chart I: TIME SCHEDULE LIFESTYLE PROGRAM)

### **WEEK 1: BASELINE EVALUATION.**

Consultation 1.

Counselling session 45-60 minutes.

Motivational counselling will include an extensive history of weight changes, knowledge and insight of weight related health problems.

Awareness, actual behaviour and lifestyle leading to overweight and history of body weight and slimming are discussed.

Counselling negative effect of overweight on frequencies of spontaneous and treatment dependent pregnancy chances and increase frequency of complications during pregnancy for mother and foetus.

The stages of change can be identified using the PACE score in the GOAL software.

DEBQ is evaluated to assess the type of eating behaviour.

Counselling and providing knowledge and advice about healthy lifestyle.

Evaluating diet questionnaire

Evaluating SQUASH score for physical activity

Healthy diet is advised aiming for a reduction of 600 Kcal/day ("Energy reduced diet"). Diet should be based on the Dutch guideline "Gezonde Voeding". Food intake should not be reduced below 1200 Kcal/day in order to achieve a sustainable lifestyle change.

Use of stepcounter is explained: 10.000 steps/day and two to three times a week sporting of at least 30 minutes of moderate intensity (60-85% of maximum heart frequency).

A questionnaire for details on indirect costs like transportation, sporting activity and productivity loss will be handed out.

Partner is involved in the counselling session

Referral to a dietician or psychologist is done in a standardized way, when appropriate.

Measuring waist circumference and weight.

### **WEEK 3: SETTING REALISTIC TARGETS AND GOALS.**

Consultation 2.

Counselling session of 45-60 minutes.

Focus on agreeing on achievable targets on an individual basis regarding physical activity, diet and body weight.

Food -and physical activity diary including results of "eetmeter" and stepcounter are evaluated. Diet: reduction of 600 Kcal/day (but not below 1200 Kcal/day) is introduced.

Physical activity aiming at 10.000 steps a day.

Patient contract describing realistic goals c.q. agreements on an individual basis regarding: weight loss (.... Kg/ .... Weeks) and physical activity (.... Steps/ .... day), and sporting activity (two to three times a week),

Plan activities to reach goals.

Address barriers and promote facilitating factors to achieve sustainable lifestyle changes.

Measuring waist circumference and weight.

WEEK 5. CONSULTATIONS VIA TELEPHONE OR MAIL (SEE BELOW)

WEEK 7: EVALUATION AND FEEDBACK

Consultation 3.

Counselling session of 30 minutes.

Regarding: motivation weight loss and physical activity.

Evaluating results regarding: bodyweight, food intake diary, "eetmeter", physical activity diary, stepcounter

Feedback on results.

Individualized advice for improvement when necessary and adjust agreements when necessary to reach realistic targets.

Discuss relapse.

Evaluating the barriers to follow the program when necessary.

Referral to a dietician or psychologist is done in a standardized way, when appropriate.

Measuring waist circumference and weight.

WEEK 8. CONSULTATIONS VIA TELEPHONE OR MAIL (SEE BELOW)

WEEK 12: EVALUATION AND FEEDBACK

Consultation 4.

Counselling session of 15-30 minutes.

Regarding: motivation weight loss and physical activity.

Evaluating results regarding: bodyweight, food intake diary, "eetmeter", physical activity diary, stepcounter.

Feedback on results.

Individualized advice for improvement when necessary and adjust agreements when necessary to reach realistic targets.

Discuss relapse.

Evaluating the barriers to follow the program when necessary.

Referral to a dietician or psychologist is done in a standardized way, when appropriate

Measuring waist circumference and weight.

A blood sample of 10 cc will be taken and serum stored

WEEK 15. CONSULTATIONS VIA TELEPHONE OR MAIL (SEE BELOW)

WEEK 18 EVALUATION AND FEEDBACK

Consultation 5.

Counselling session of 15-30 minutes.

Regarding: motivation weight loss and physical activity

Evaluating results regarding: weight, food diary, eetmeter, physical activity, stepcounter, -

Feedback on results.

Individualized advice for improvement when necessary and adjust agreements when necessary to reach realistic targets.

Discuss relapse.

Evaluating the barriers to follow the program when necessary.

Referral to a dietician or psychologist is done in a standardized way, when appropriate.

Measuring waist circumference and weight.

#### WEEK 21. CONSULTATIONS VIA TELEPHONE OR MAIL (SEE BELOW)

##### WEEK 24 EVALUATION OF TARGETS

Consultation 6.

Counselling session of 15-30 minutes.

Evaluation of targets:

Weight reduction

Physical activity

Behaviour change

Measuring waist circumference and weight.

A blood sample of 10 cc will be taken and serum stored.

#### CONSULTATIONS VIA TELEPHONE OR MAIL WEEK 5, 8, 15, AND 21.

In between the consultations in the outpatient fertility clinic, consultation via telephone or mail are scheduled at week 5, week 9, week 15, and week 21 with a duration of 15 minutes. In these consultations evaluation regarding: motivation of weight loss and physical activity are discussed

Evaluating results regarding: weight, food diary, eetmeter, physical activity, stepcounter.

Feedback on results.

Individualized advice for improvement when necessary and adjust agreements when necessary to reach realistic targets.

Discuss relapse.

Evaluating the barriers to follow the program when necessary.

Questionnaires for all included women: SF36, FFQ and Squash-list will be evaluated at the start and week 12 and week 24 and 52 weeks after randomisation.

#### Start of fertility treatment

When in spontaneous ovulatory patients in the lifestyle intervention arm:

- have finished their six month lifestyle program or,
- when they meet their target weight reduction of 5-10% or,
- when their weight decreases < BMI 29 kg/m^2,

fertility treatment will be started if the individual prognosis, based on the Hunault model (Hunault et al.2004) if less than 30% chance of conception within one year or when more than 3 years subfertility (guideline NVOG) justifies starting treatment (either IUI, IVF or ICSI (according to national guidelines NVOG).

In case of chronic anovulation, ovulation induction will be started when patients in the lifestyle intervention arm:

- have finished their six month lifestyle program or,
- when they meet their target weight reduction of 5-10% or,
- when their weight decreases < BMI 29 kg/m^2.

**Table 1: time schedule lifestyle intervention**

| Week | Consultation
Outpatient/
Telephone or mail | Counseling subject lifestyle program                                                                                | Duration
minutes |
|-------------|-----------------------------------------------------------|----------------------------------------------------------------------------------------------------------------------------|-----------------------------|
|             | Randomisation                                             | Baseline assessment and explanation lifestyle program; handout of "eetmeter", stepcounter and diary . Blood sample (10 cc) | 30                          |
| 1           | Outpatient 1                                              | Setting targets and planning goals; evaluating baseline measures , hand out of cost-questionnaires                         | 45-60                       |
| 3           | Outpatient 2                                              | Evaluating targets;                                                                                                        | 45-60                       |
| 5           | Telephone 1                                               | Evaluating targets                                                                                                         | 15                          |
| 7           | Outpatient 3                                              | Evaluating targets                                                                                                         | 30                          |
| 9           | Telephone or mail 2                                       | Evaluating targets                                                                                                         | 15                          |
| 12          | Outpatient 4                                              | Evaluating targets, handout of questionnaires
Blood sample (10 cc)                                                      | 30                          |
| 15          | Telephone or mail 3                                       | Evaluating targets                                                                                                         | 15                          |
| 18          | Outpatient 5                                              | Evaluating targets                                                                                                         | 30                          |
| 21          | Telephone or mail 4                                       | Evaluating targets                                                                                                         | 15                          |
| 24          | Outpatient 6                                              | Assessing targets and evaluation lifestyle program and handout of questionnaire                                            | 30                          |
| >24         | Outpatient                                                | Start infertility treatment when applicable
Blood sample (10 cc)                                                        |                             |
| 52          |                                                           | questionnaires                                                                                                             |                             |

#### **6.4 Withdrawal of individual subjects**

Subjects can leave the study at any time for any reason if they wish to do so without any consequences. Patients who decide to withdraw from the study will be asked by the responsible investigator to provide information regarding the primary endpoint of the study 24 months after randomisation. Patients who drop out of the study will be treated according to the local protocols for infertility patients.

The investigator can decide to withdraw a subject from the study for medical reasons.

Women who miss two consecutive counselling sessions and who are not willing to catch up are excluded from the program.

## **7. SAFETY REPORTING**

### **7.1 Section 10 WMO event**

In accordance to section 10, subsection 1, of the WMO, the investigator will inform the subjects and the reviewing accredited METC if anything occurs, on the basis of which it appears that the disadvantages of participation may be significantly greater than was foreseen in the research proposal. The study will be suspended pending further review by the accredited METC, except insofar as suspension would jeopardise the subjects' health. The investigator will take care that all subjects are kept informed.

### **7.2 Adverse and serious adverse events**

Adverse and serious adverse events as a direct result of the lifestyle intervention are not anticipated in this study. However, patients with overweight or obesity have additional risks during pregnancy compared to normal weight women. As a result of both the intervention arm and of the "care as usual" arm, pregnancies may occur in patients with increased risks. The risks involve hypertension (OR: 2.2), preeclampsia (OR: 1.8-2.7), pregnancy-induced diabetes (OR: 2.2-3.4), caesarian section (OR: 1.3-2.4) (see tables of evidence in appendix). These risks are not influenced by fertility treatment. Lifestyle intervention aims to reduce the involved pregnancy risks. Participants in the study have been informed about these risks. An independent Safety Monitoring Board (SMB) will be installed to review major complications in both treatment groups. This board will evaluate complications after every 150 included patients and six months and 12 months after the end of inclusion of the study (6 times during the study). The SMB will differentiate between major en minor complications, blinded for treatment arm. Every case of preeclampsia, eclampsia, HELLP syndrome, will be reported to the SMB. The SMB findings will be reported to the Ethics Committee of the UMCG

Adverse events are defined as any undesirable experience occurring to a subject during a clinical trial, whether or not considered related to the investigation. All adverse events reported spontaneously by the subject or observed by the investigator or his staff will be recorded.

A serious adverse event is any untoward medical occurrence or effect that at any dose results in death;

- is life threatening (at the time of the event);
- requires hospitalisation or prolongation of existing inpatients' hospitalisation;
- results in persistent or significant disability or incapacity;
- is a congenital anomaly or birth defect;

- is a new event of the trial likely to affect the safety of the subjects, such as an unexpected outcome of an adverse reaction, lack of efficacy of an IMP used for the treatment of a life threatening disease, major safety finding from a newly completed animal study, etc.

All SAEs will be reported to the accredited METC that approved the protocol, according to the requirements of that METC.

### **7.3 Follow-up of adverse events**

All adverse events will be followed until they have abated, or until a stable situation has been reached. Depending on the event, follow up may require additional tests or medical procedures as indicated, and/or referral to the general physician or a medical specialist.

## **8. STATISTICAL ANALYSIS**

### **8.1 Descriptive statistics**

To assess whether the groups were balanced the study population will be compared for baseline measurements including female age, type of subfertility (primary or secondary), duration of subfertility, intoxications, smoking, BMI, as well as sperm analysis according to WHO standards, anovulation, and subfertility treatment. Confounding factors, such as smoking, education, ethnicity will be addressed in the analysis.

### **8.2 Univariate analysis and multivariate analysis**

The primary analysis will be by intention to treat.

The primary outcome will be analysed by comparing the pregnancy rates in both groups using Kaplan-Meier analysis of time to pregnancy using the Log-rank test. In this analysis, patients will be censored at the time they discontinue or complete the study without getting pregnant. In addition, pregnancy rates and 95% confidence intervals per group will be calculated based on the Kaplan-Meier estimates at various time points. Further analysis of delivery rates over time will be performed using Cox-regression analysis with correction for the stratification variables ovulatory status and treatment centers as well as for confounders. These analyses will also be performed for spontaneous and treatment-induced pregnancies separately. The same analysis will be performed for the secondary outcome ongoing pregnancies. This will include ongoing pregnancies, that have not yet resulted in the birth of a child. Exploratory subgroup analyses of the primary outcome will be performed for spontaneous and treatment-induced pregnancies and for women with a BMI below 35 versus above 35, as well as for anovulatory versus ovulatory women and for women with a waist-hip ratio of above 0.8 versus below or equal to 0.8 and for women who are 36 years or older versus younger than 36 years based on tests of interaction with treatment group.

Additional analysis concerning the influence of HOMA, androgens, adipokines and cytokines on pregnancy chances and recovery of ovulations in anovulatory patients will be assessed using multivariate Cox-regression.

Incidence of complications of treatment and during pregnancy will be compared in both groups using relative risks and 95% confidence intervals.

Quality of life will be analysed using repeated measures analysis of variance

A per protocol analysis will also be performed, in which drop out patients will be identified as non-compliant. Information on the primary outcome, i.e. lifebirth within two years after randomisation will be used whenever provided. Patients who drop out of the lifestyle intervention arm will be analysed in the “usual care” arm in this per protocol analysis.

Women who drop out of the study will be asked to provide the reason for dropping out. This reason will be recorded and patients will be asked to provide information regarding the primary outcome, i.e. pregnancy within two years after randomisation. In addition, patients will be offered the possibility to continue to complete cost questionnaires for the remainder of the study duration. For patients dropping out of the lifestyle intervention, further course will be determined by the responsible physician.

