**Main study parameters/endpoints:**

Primary endpoint is the birth of a healthy singleton after vaginal delivery of at least 37 weeks gestation.

Secondary outcome parameters are number of fertility treatments (OI, IUI, IVF, ICSI), quality and amount of oocytes and embryos and cryo embryos derived in an IVF or ICSI procedure, the amount of embryos per transfer, implantation rate of transferred embryos, complications of fertility treatment, clinical and ongoing pregnancy rates, perinatal outcome, complications and quality of life as well as body weight, waist circumference, behaviour influencing weight, i.e. nutritional habits and exercise pattern, smoking habits, blood pressure, glucose/insulin ratio (HOMA), hormonal profile and costs.

**DATA ANALYSIS:** Analysis will be by intention to treat. Randomisation will be stratified for the presence or absence of anovulation and per treatment center. We expect an

improvement in vaginal singleton delivery beyond 37 weeks from 45% to 60%. Anticipating drop out of 20% in the intervention arm and a 5% loss to follow up in the study, we need to include two groups of 285 women (two-sided test, alpha error .05, beta-error .20).

**STUDY DURATION:** Preparation of the study, including the training of the nurses, will take three months. Inclusion of the couples will take 24 months and the lifestyle intervention will take six months. Follow up is continued for 24 months after randomisation. Database cleaning and analysis of the study will take 6 months. Duration of the study: 57 months

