#### **4.4 Sample size calculation**

**SAMPLE SIZE:** On the basis of the literature the cumulative live birth rate in a follow up of two years of subfertility treatment will be 45% for the “usual care” group (Dutch OFO-study, unpublished data). The lifestyle intervention group is estimated to have a live birth rate of 60% (Dutch OFO-study, unpublished data)

We expect an improvement of healthy singleton of more than 37 week gestation born after vaginal delivery from 45% to 60% in the intervention group. Drop out is expected to be 20% in the intervention arm and is included in the analysis of effectiveness.

To prove that, we need to include two groups of 272 women to be included (alpha 0.05, power 80%). To account for 5% lost to follow up 285 women will be included per group. In total 570 women will be included.

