### 4.2 Study design

The study is a multicenter randomized clinical trial. Subfertile women (age 18-39) with a BMI of 29 kg/m^2 or above will be included. Exclusion criteria are: azoospermia or donor semen, severe endometriosis, chronic anovulation due to WHO III and endocrinopathies. Women with an untreated pre-existent hypertension or diabetes type 1, or pregnancy-induced hypertension, preeclampsia, eclampsia or HELLP syndrome in a previous pregnancy are excluded.

The intervention consists of a structured lifestyle program of six months, which aims at realistic weight loss of at least 5% to 10%, achieved by the combination of a healthy diet (caloric reduction of 600kCal/day), increase of physical activity (aiming at 10.000 steps per day) and two to three times a week sporting activity, and behavioral modification. The structured lifestyle program, in which practice variation is minimized using a structured software program, has been developed, used and evaluated previously (Zon-MW project 50-

50110-98-078; the Groninger Overweight And Lifestyle study (GOAL)). After six months of lifestyle intervention patients will start fertility treatment as indicated.

In the “usual care” arm fertility treatment will be started if this is justified by the individual prognosis (guideline NVOG)

All randomized women will fill in questionnaires concerning: diet, eating behavior, physical activity and smoking: SF-36, FFQ, DEBQ, Squash list, at inclusion, and at 12 weeks, 6 months, 12 months and 24 months after randomization. Blood samples (10 cc) will be taken at the start, 3 months and 6 months after the start of the study.

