#### 5.1.3 Secondary efficacy endpoints

Secondary outcome parameters are:

1. Pregnancy outcome and -complications: miscarriage, gestational diabetes, Pregnancy induced hypertension, preeclampsia, HELLP, prematurity < 37 weeks, macrosomia (> p90 (Large for Gestational Age), induction of labour, prolonged duration of labour, operative delivery, assisted delivery and increased blood loss, and multiple pregnancies
2. Percentage of women needing fertility treatment in both groups (OI, IUI, IVF, ICSI) and ongoing pregnancy rates in these treatments.

3. Quality and number of oocytes and embryos and cryo embryos resulting from an IVF or ICSI procedure and the amount of embryos per transfer and implantation rate of transferred embryos
4. Complications during fertility treatment: ovarian hyperstimulation syndrome, infection, tubal pregnancies, torsion (etc).
5. Perinatal outcome: stillbirth, pregnancy duration, body weight, Apgar scores, arterial pH, congenital anomalies and neonatal admission to a neonatal medium, high or intensive care unit.
6. Quality of life, pre-pregnancy body weight, weight gain during pregnancy, waist circumference, behaviour influencing weight, i.e. nutritional habits and exercise pattern, blood pressure, glucose/insulin ratio (HOMA), hormonal profile (androgens, adipokines and cytokines) and costs.

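### Quality of life is assigned to repeated measures ANOVA with no missing-data rule, although drop-out is expected mainly in one arm and the visit list is inconsistent

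*Supplement*

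**What the plan says.** **Outcome and method.** SAP 5.1.3 (item 6) lists "Quality of life, pre-pregnancy body weight, weight gain during pregnancy, waist circumference, behaviour influencing weight" among the secondary outcomes. Protocol 8.2 states "Quality of life will be analysed using repeated measures analysis of variance" and nothing more: no model terms, no contrast, no rule for missing scores. SAP sections 6.4 to 6.7 do not mention quality of life. The SF-36 is the only listed questionnaire that fits, and I take it to be the instrument, although protocol 5.1 describes it as a satisfaction measure.

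**Drop-out.** Protocol 4.4 says "Drop out is expected to be 20% in the intervention arm and is included in the analysis of effectiveness". The Summary has "Anticipating drop out of 20% in the intervention arm and a 5% loss to follow up in the study". Women who withdraw are asked, under protocol 6.4, to "provide information regarding the primary endpoint of the study 24 months after randomisation". Section 8.2 asks drop-outs for their reason and primary outcome, and adds that "patients will be offered the possibility to continue to complete cost questionnaires for the remainder of the study duration". Neither place mentions the SF-36.

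**Visits.** Protocol 5.1 (Follow-up) has "Questionnaires will be completed at start, 12 weeks, 24 weeks and 52 weeks after randomisation". SAP 4.2 has "at inclusion, and at 12 weeks, 6 months, 12 months and 24 months after randomization".

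**The concern.** Classical repeated measures ANOVA takes one complete row per woman, so a woman with any missing visit is left out. If women who leave the lifestyle arm also stop returning the SF-36, its analysed group is the women who stayed, set against nearly all usual-care women. Should women who feel worse be more likely to leave, the comparison tilts towards lifestyle even if the programme has no effect on quality of life. Precision is lost in any case, because the early scores of incomplete women are discarded.

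The visit conflict adds to this. Under complete-case analysis, the number of scheduled visits decides who is analysed.

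**Working it through.** **1. Is unequal drop-out the plan's own assumption?** Diluting the intervention rate by 20% drop-out gives 0.80 × 0.60 + 0.20 × 0.45 = 0.57. For 45% v 57%, two-sided alpha 0.05 and 80% power, the pooled-variance formula is

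n = [1.960 × √(2 × 0.51 × 0.49) + 0.842 × √(0.45 × 0.55 + 0.57 × 0.43)]² / 0.12² = 271.2, rounded up to 272.

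This matches the stated 272 per group; undiluted 45% v 60% would give 173. Also 272 × 1.05 = 285.6, in line with the stated 285. So the one-sided 20% is built into the plan.

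**2. What it would mean for the SF-36.** Assumption: programme drop-outs stop completing it.
- Usual care: 285 × 0.95 = 270.75, about 271 complete.
- Lifestyle: 285 × 0.95 × 0.80 = 216.6, about 217 complete (24% missing).
- Total: 487.35 of 570, or 85.5%.

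For an assumed true difference of 0.25 SD at a single visit, power is 83% with 271 per arm and 78% with 271 v 217.

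**3. Bias with no true effect.** Simulation assumptions: 285 per arm, four visits, equal correlation 0.6 between visits, and drop-out after week 12 of 24% (lifestyle) and 5% (usual care, at random). In the lifestyle arm the log-odds of drop-out rise by 0 to 1.0 for each SD that the week-12 score is lower. The documents give none of these association values. All-visit completers are analysed.

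| Contrast | Bias (SD) | Type I error |
|---|---|---|
| Last visit | 0 to about 0.13 | 5% to 28% |
| Group main effect, mean over visits | 0 to about 0.15 | 5% to 48% |
| Change, baseline to last visit | about 0 | 5% to 6% |

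At the middle value of 0.5, the group main effect has a bias of about 0.08 SD and a type I error of about 19%. If the 5% drop-out in usual care depends on week-12 score in the same way, the biases are smaller: at log-odds 1.0, about 0.09 SD (last visit) and 0.11 SD (main effect).

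Change from baseline escapes because, with equal correlations, selection on the week-12 score shifts the baseline and last-visit means by the same amount.

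A likelihood-type estimate predicts the last visit from baseline and week 12 and averages over all women. Its bias is about 0 throughout. That follows from the set-up: drop-out depends only on an observed score, which is missing at random.

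**4. Visit lists in the current versions.**

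| Place | Last SF-36 |
|---|---|
| Protocol Summary, Intervention | 24 months |
| Protocol Summary, burden and risks | week 52 |
| Protocol 5.1, Follow-up | week 52 |
| Protocol 6.3, after the telephone consultations | week 52 |
| Protocol Table 1 | week 52 |
| SAP 4.2 | 24 months |

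If each post-baseline visit were missed independently with probability m, the complete share is (1 − m)³ with three post-baseline visits and (1 − m)⁴ with four. For an assumed m of 5% to 15%, that is 86% to 61% against 81% to 52%.

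**The case against.** Four objections have force.

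- **Deletion is not written down.** A reader might infer that every woman with one missing visit will be dropped. The protocol names no software, model form or deletion rule, and the term is sometimes used loosely for a mixed model. What stands is that the classical procedure deletes incomplete cases and nothing in either document rules it out.
- **The 20% is not an SF-36 non-response rate.** It is drop-out in the lifestyle arm, and those women remain in the primary analysis. Women who miss sessions leave the programme, not expressly the study. Questionnaires go to both arms, by web or on paper, and are not tied to sessions. So the loss of SF-36 scores in step 2 is plausible but inferred.
- **Unequal drop-out is not bias in itself.** A reader might infer that the comparison is certain to be biased. If drop-out is unrelated to quality of life, bias is nil and type I error is 5%. The documents do not say that the two are related, and the result depends on the contrast reported, which the plan does not name. The group-by-time test in similar runs rose from 5% to 16%, less than the main effect.
- **A mixed model is not a cure-all.** If drop-out depends on unobserved scores, it is biased too.

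These points limit the claim to a possible bias of uncertain size. They leave in place the missing rule, the expected imbalance and the conflicting visits. Nor is the conflict simply Summary and SAP against the body of the protocol: the Summary contradicts itself.

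**Conclusion.** The point holds in this form. The only stated method for a named secondary outcome ordinarily discards incomplete cases, no missing-data rule accompanies it, drop-out is expected mainly in one arm, and post-drop-out collection does not mention the SF-36. Precision is lost if scores are missing, and bias is possible if drop-out is related to quality of life.

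The range of bias and type I error in step 3 rests on assumed drop-out of 24% v 5%, correlation 0.6 and an assumed link to the week-12 score. It shows how far the result could move and does not predict what will happen. The visit conflict is a plain inconsistency within the latest protocol and between it and the SAP.

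The sponsor should amend this. The primary outcome, its sample size and its analysis are unaffected.

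**What to change.** Replace the sentence in protocol 8.2, and repeat the new one in the SAP:

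'SF-36 scores will be analysed with a linear mixed model for repeated measures using all available scores, with baseline score, ovulatory status, centre (fixed or random), visit, arm and arm-by-visit as terms.'

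Ovulatory status and centre are the stratification factors. The model needs no new data. Its small downside is reliance on missing at random, which the text should acknowledge.

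Then use one questionnaire schedule in both Summary paragraphs (Intervention; burden and risks), protocol 5.1, 6.3 and Table 1, and SAP 4.2, stating whether there is a 24-month SF-36. If it is kept, it can go out with the cost questionnaire already planned for the end of follow-up. The cost is one sentence in each document and an editorial correction of the visit list.
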